shipment inventory. Any damaged or unusable nabilone in a given pick-up will be documented in the clinical trial files. Regarding dispensing the study medication, participants/caregivers will come to CAMH at 3 separate times to pick up nabilone (Table 1), including 1) to pick up the package for the whole dose titration phase and the first 6 days of the stable dose phase at the Pre-treatment Visit (V 0), 2) to pick up the package for the remaining days of the stable phase, and 3) to pick up the package for the dose tapering phase at the Post-treatment Visit (V 1). Nabilone will be prepared for each visit by Research Pharmacy Service. Participants/caregivers will be requested to document the details of using nabilone and other concomitant medications in the drug diary. They will also be asked and expected to return the empty or any leftover nabilone back to the study team, to help with drug accountability.

Regular study intervention reconciliation will be performed to document nabilone assigned, consumed, and remaining. This reconciliation will be logged on a drug accountability log, and signed and dated by delegated research and/or pharmacy staff.

At the completion of the clinical trial, there will be a final reconciliation of the nabilone dispensed, consumed and remaining, based on the drug diary, the remaining drugs which are returned. This reconciliation will be logged on an accountability form, and signed and dated by delegated research and/or pharmacy staff. Any discrepancies noted will be investigated, resolved, and documented prior to return or destruction of unused study intervention. Intervention destroyed on site will be documented in the clinical trial's files.

All participants entering the dose titration phase will be included in the description of the safety profile and tolerability of nabilone (the Primary Objective). Participants completing the dose titration stage will be included in the final statistical analysis for the Exploratory Objective (i.e., explore changes in SBP in participants pre-and post-treatment), regardless of whether they complete the full protocol. This approach is consistent with the intention-to-treat principle.

**Figure 1.** A schematic diagram of the study procedures, including all study visits and timelines. Abbreviation: S-V: a screening visit; V 0: a baseline visit; V 1: a visit at the end of open label phase; V-F: a follow-up visit to ensure safety; d: days; wk: weeks; FU: follow-up; max: maximum.

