## **8. SAMPLE SIZE AND DATA ANALYSIS**

To test the Hypotheses 1 and 2, we aim to enroll 40 patients to enter the dose titration phase, consistent with common sample sizes for Phase I trials (63).

We assume the attrition rate of 25% from the dose titration phase to entering the open-label phase. To test behavioural changes at the group level (Exploratory Objective), the sample size of the remaining participants (N=30) could be sufficient to detect differences with effect size Cohen's d as low as of 0.53, and at power = 0.8 and two-sided  $\alpha$ -level = 0.05 (G\*Power 3.1), which is similar to that detected in the study investigating the effects of nabilone on agitation associated with dementia (27).

Paired-t test will be used to investigate the pre- vs. post-treatment behavioural and brain changes. Exploratory analyses will be performed to determine predictors of response including baseline individual features, using logistic regression. Safety profiles will be described in the percentage of each adverse effects. For MRI measures, non-parametric tests will be used to explore the brain changes with nabilone treatment, assuming that only few participants can finish MRI scans eventually.

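### The behavioural analysis set is conditioned on completing titration yet labelled intention-to-treat, and no behavioural score is collected from participants who leave before V 1

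*Protocol*

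**What the plan says.** Protocol section 3.1 defines two analysis sets. Everyone who enters titration counts for safety and tolerability, the primary objective. For the behavioural question, "Participants completing the dose titration stage will be included in the final statistical analysis for the Exploratory Objective", whether or not they finish the rest of the protocol. The section then adds: "This approach is consistent with the intention-to-treat principle".

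Section 8 gives the numbers: "we aim to enroll 40 patients to enter the dose titration phase", and "We assume the attrition rate of 25% from the dose titration phase to entering the open-label phase". The remaining 30 are said to be "sufficient to detect differences with effect size Cohen's d as low as of 0.53" "at power = 0.8 and two-sided" alpha of 0.05. The test is named: "Paired-t test will be used to investigate the pre- vs. post-treatment behavioural and brain changes".

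Table 1 and section 3.2 place ABC-I at screening, V 0 and V 1, and MOAS at V 0 and V 1. Neither scale is scheduled during titration, during the open-label phase or at the safety follow-up. Section 7.1 gives withdrawn participants the same safety follow-up visit as completers and otherwise stops data collection.

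**The concern.** Intention-to-treat means analysing everyone who was to be treated, whatever happened afterwards. In a single-arm trial the natural counterpart is everyone who starts the drug. Completing titration happens after the first dose and can depend on how the participant fares on the drug. A set chosen on that event is a selected subset of the treated participants, and the protocol already names the all-treated set for its primary objective.

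A second problem lies behind the label. The protocol promises to keep titration completers who do not finish, but someone who leaves before V 1 has no post-baseline behavioural score, and a paired t-test cannot use a participant without one. In practice the analysed set is titration completers with a V 1 rating.

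At stake is what the pre-post change in severe behavioural problems may be said to show. Sections 1.1 and 2 say the findings will inform the design of later controlled trials. A change labelled intention-to-treat but estimated in those who stayed could be read as the change to expect in everyone started on nabilone.

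**Working it through.** **1. The plan's own figure.** Inputs from section 8: n = 30, two-sided alpha 0.05, power 0.80. The test is a paired t-test, with power taken from the noncentral t with n - 1 = 29 degrees of freedom and noncentrality d × √n. Solving for power 0.80 gives d = 0.529; at d = 0.53 the power is 0.801. The stated 0.53 reproduces. Attrition: 40 × (1 - 0.25) = 30, so 10 treated participants are left out of the behavioural analysis by plan.

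**2. Can leavers be kept?** Setting the sections side by side:
- Leaves during titration: excluded by the set definition in section 3.1.
- Completes titration, leaves before V 1: included by definition, but has no post-baseline ABC-I or MOAS (Table 1) and is offered only a follow-up visit without those scales (sections 3.2 and 7.1). The paired test drops this person.
- Attends V 1, misses the taper or the safety follow-up: has both scores and is kept. Here the promise holds.

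**3. What the selection could do to the estimate.** Let improvement be positive, in units of the within-group SD of change. Take 0.53 in those retained, purely as a reference value because it is the only effect size in the plan. Let m be the mean change in those lost; the protocol gives no figure, so m is an assumption shown over a range.

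All-treated mean change = 0.75 × 0.53 + 0.25 × m

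Mixture SD = √(1 + 0.75 × 0.25 × (0.53 - m)²)

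| m (assumed) | All-treated mean change | Retained ÷ all treated | Standardised d |
|---|---|---|---|
| +0.53 | 0.530 | 1.00 | 0.53 |
| +0.25 | 0.460 | 1.15 | 0.46 |
| 0 | 0.3975 | 1.33 | 0.39 |
| -0.25 | 0.335 | 1.58 | 0.32 |
| -0.53 | 0.265 | 2.00 | 0.24 |

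For m = 0: 0.75 × 0.53 = 0.3975; SD = √(1 + 0.1875 × 0.2809) = 1.026; d = 0.3975 / 1.026 = 0.387.

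**4. Loss after titration.** The 30 makes no allowance for it. With an assumed further loss of 5%, 10% or 20% before V 1, 28, 27 or 24 pairs remain, and power at d = 0.53 falls from 0.801 to 0.771, 0.755 or 0.701.

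**The case against.** The strongest reply is that this is an exploratory objective, that the completer set is stated openly and powered on 30, and that the primary set already includes everyone who enters titration. That is right, and it limits the weight of the point: no primary result changes.

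A second reply is that handling of missing V 1 scores usually belongs in a statistical analysis plan, which is not shown. That stands for the choice of method. It does not remove the point, because the analysis set and its label are fixed in the protocol, and no analysis plan can supply ratings that the visit schedule never collects.

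Three stronger readings are tempting but not supported:
- A reader might infer that the plan is shown to overstate improvement, by a quarter or a third. The direction is an inference and the size depends wholly on m. Zero change is not a neutral value either: entry requires an ABC-I score of at least 18, so regression to the mean could bring some improvement in those lost as well.
- A reader might infer that everyone who cannot tolerate the drug is removed. Section 3.1 sends participants with intolerable effects into the open-label phase at the previous dose, so they stay in the set. The 25% is attrition of unstated cause, and section 7.1 also lists loss to follow-up and withdrawn consent.
- A reader might infer that the next trial will be undersized. The protocol says only that findings inform later designs. Moreover, 0.53 is a detectable effect rather than an expected one, and the power of a paired single-arm test does not carry over to a placebo-controlled trial.

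**Conclusion.** The behavioural set is selected on a post-treatment event and is not intention-to-treat; the label is wrong on the protocol's own definitions. By the plan's own assumption it omits 10 of 40 treated participants (25%). The promise to include titration completers cannot be met for those who leave before V 1. That last step rests on reading the visit schedule, the withdrawal rule and the named test together; the protocol does not itself restrict the set to people with a V 1 score.

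The pre-post change is too favourable for the treated population if those lost improve less than those retained. That is likely but not demonstrated. In the illustration the excess runs from none to a factor of two over the assumed range of m. Because only the exploratory objective is touched, this should be fixed but does not undermine the trial's primary aim.

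**What to change.** Define the main behavioural analysis set as all participants who start nabilone. Report titration completers as a secondary set, without the intention-to-treat label.

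Add a caregiver ABC-I and MOAS rating when nabilone is stopped early. Section 3.4 puts these at under 10 and under 5 minutes, so under 15 together, and Table 1 allows both to be done remotely. State the recall period as time since starting the drug. The four-week window used at screening and baseline would otherwise reach back before the first dose, by at least 28 - 15 = 13 days for someone who leaves within the 15-day titration. Reconcile this rating with sections 4 and 7.1, which say that data collection ends on withdrawal.

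Add a sensitivity analysis for missing V 1 scores, for example zero change together with a range on either side.

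If none of this is adopted, delete the intention-to-treat sentence and describe the result as applying to titration completers with a V 1 rating.

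The cost is an amendment to section 3.1, section 7.1 and Table 1, with the matching participant information; a few minutes of caregiver time; early-stop ratings that cover a shorter period than the V 1 ratings; and probably a smaller effect estimate.

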### 3.2. Assessments and visits (Table 1):

Screening assessments for participants and their caregivers include:

- Assessment of prior medical records to collect information of previous cognitive assessment regarding IQ, status of Disability of Ontario Services (DSO), co-occurring physical and psychiatric diagnoses, medication use and potential changes.
- Assessment of capacity to make an informed consent based on both the MacArthur Competence Assessment Tool for Clinical Research (MacCAT-CR) (44) and clinical assessment (45). This will be carried out before the informed consent process and formal assessment.
- Interview of the Moss Psychiatric Assessment Schedules (Moss-PAS (ID)) to the caregiver to assess for co-occurring mental health conditions.
- The Adaptive Behavior Assessment System, Third Edition (ABAS-3), Adult Form, will measure adaptive behaviour and function.
- Measuring of vital signs, weight and height.
- Urine pregnancy test for sexually active women of child-bearing potential.
- Caregiver rated Aberrant Behavior Checklist-Irritability subscale (ABC-I) will be used to define the SBP. Clinical Global Impression – Severity scale (CGI-S) will be rated by the investigator to evaluate the severity of the behavioural problems.

Baseline (pre-treatment) assessments include:

- Measuring of vital signs and weight.
- Assessment of participants' cognitive capacity using the NIH Toolbox® Cognition Battery.
- Assessment of SBP of participants using the ABC-I and MOAS, and anxiety using the General Anxiety Subscale of the ADAMS, as reported by the caregivers.
- Assessment of caregiver's stress and crisis using the Stress Subscale of DASS-21 and BFDS.
- Exploratory assessment of autism symptoms using the Social Communication Questionnaire for Adults with Intellectual Disability (SCQ-AID).

- Optional assessment of MRI Imaging (dependent on the participant's ability to comply with the following assessments, in the opinion of the carers/parents and investigator).
- Concomitant medication

Post-treatment assessments include:

- Assessment of adverse events using the UKU side effect rating scale, examined by the researcher or investigator.
- Re-measuring of vital signs and weight.
- Re-assessment of participants' cognitive capacity using the NIH Toolbox® Cognition Battery.
- Re-assessment of caregiver rated ABC-I, MOAS, General Anxiety Subscale of ADAMS. CGI-S and CGI-I will be rated by the investigator to evaluate the severity and improvement of the behavioural problems after nabilone treatment.
- Re-assessment of caregiver's stress and crisis using the Stress Subscale of DASS-21 and BFDS.
- Optional re-assessment of MRI Imaging for those who finish the pre-treatment MRI and are willing to receive the second wave of MRI imaging.
- Concomitant medication

Safety follow-up assessments include:

- Re-assessment of adverse events using the UKU side effect rating scale, examined by the researcher or investigator.
- Re-measuring of vital signs and weight.
- Concomitant medication
- Re-assessment of participants' cognitive capacity using the NIH Toolbox® Cognition Battery.
- Assessment of caregivers' acceptability of the study protocol using the custom-designed questionnaire, as completed by the caregiver.

### Elective Virtual Assessment

To reduce barriers associated with traffic and time and to future-proof the research protocol in case of another COVID lockdown, we will provide the option for virtual assessments. As shown in the last column of Table 1, interviews that collect data on demographics, clinical history, diagnoses alongside medication use, competence, and adverse effects can be conducted virtually using teleconferencing/videoconferencing software (Webex). Additionally, a blank paper copy of outcome measures rated by caregivers (including the ABC-I, MOAS, Anxiety-ADAMS, Stress-DASS-21, BFDS, and SCQ-AIQ) can be electively sent to them via mail. Completed questionnaires can be mailed, faxed, scanned, or photographed back to the study team. If the caregivers choose to send the completed questionnaire by mail, we will provide a pre-paid postage envelope.

The virtual sessions will be undertaken in coordination with in-person sessions based on the same research standards. The participants and caregivers can flexibly choose either the in-person or virtual assessments for those elective options (Table 1). We will notify both the participant and their caregiver of this virtual option when explaining the study (based on the Telephone Contact Script) and discussing the informed consent.

If the participant/SDM/caregiver chooses to have a virtual informed consent process (as detailed in Section 5) and virtual screening assessment, we will only start the assessment after we receive

the signed informed consent form (with wet signatures). To reduce the barriers by enhancing the convenience and flexibility of participants/caregivers, if they choose to have screening assessments done virtually, the measures of the Screening Visit which require in-person assessments (i.e., pregnancy test, height, vital signs and physical examination) will be carried out in combination with those implemented during the pre-treatment assessment (V 0).

During virtual visits, the study team will document the records of virtual assessment on a study computer and sign the documents with e-signature first when working remotely. Then the person(s) who implements the virtual assessment will then print out the e-signed records and add a wet signature to verify the sources at first available opportunity on-site.

### **3.3 Selection Criteria**

#### Inclusion Criteria

Participants of any sex or gender, race or ethnicity meeting all criteria listed below will be included in the study:

- 1) Aged  $\geq 25$  years, as medical cannabis should not be used in any person aged  $< 25$  as suggested by Health Canada (24).
- 2) Adults with a DSM-5 diagnosis of ID meeting: a. Full scale IQ  $< 70$  on a standardized cognitive assessment reported in their prior medical record; b. A deficit in adaptive function in at least one activity of life, as estimated by the Adaptive Behavior Assessment System, rated by the caregiver. For those whose verified records are not available, they are deemed eligible if they are connected with Disability Services Ontario. People with ID and other developmental disabilities, e.g., autism, Down syndrome, genetic conditions such as Angelman syndrome, fragile X syndrome, Prader-Willi Syndrome, etc., will also be enrolled.
- 3) SBP, including aggressive, disruptive, and/or self-injurious behaviours in any situation (home, day program, clinic, etc.), defined as a score  $\geq 18$  on the Aberrant Behaviour Checklist-Irritability subscale (ABC-I), and a score  $\geq 4$  on the Clinical Global Impressions-Severity scale (41). A consistent pattern of frequent SBP should occur for  $> 3$  months  $\geq 1$  time per week.
- 4) Sexually active women of child-bearing potential must have a negative urine pregnancy test at the screening visit.
- 5) Sexually active women of child-bearing must use an effective method of birth control at least from the start of last two normal menses before the screening visit to one month after the end of the study (completion of the safety visit). The accepted methods of contraception include total sexual abstinence, if it is the usual and preferred lifestyle, or consistently and correctly taking the oral hormonal contraceptive.
- 6) Adults who receive a blood test in recent 12 months, which shows liver function test with the ALT  $\leq 3$  times the upper limit of normal and bilirubin  $\leq 2$  times the upper limit of normal.
- 7) At least one month that needs to pass from the participation in another investigational drug trial to a given adults being allowed to participate in this trial.

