After V 0, eligible participants will receive open-label nabilone starting with a dosage of 0.25 mg before sleep. During the dose titration phase (which could last up to 15 days), nabilone will be titrated in 0.25 mg increments every two days (with the dosing schedule "twice daily") after consultation with the study team during regular phone calls. This proposed up-titration schedule was decided based on a clinical trial of using Nabilone to treat non-motor symptoms in adults with Parkinson's disease (30). These regular phone calls will be carried out every two days during the whole dose titration phase until the participant reaches a stable dose for the open-label phase. The study team will also check whether the participants show any physical or mental changes which are believed to be attributed to AEs (based on the UKU side effect rating scale), and advise the participant and their caregivers on the next step of titration accordingly. Dose adjustments are

performed until the participant reaches the maximum permitted dose of 1 mg twice daily or experience intolerable AEs believed to be related to nabilone. If intolerable, the participant will use nabilone at the previous lower dose, entering the open label phase. Note that the suggested maximum nabilone daily dose per the product monograph is 6 mg. However, considering the vulnerability of the current target population, we choose to administer 2 mg/day at most in the current proposal following the maximum dose used in clinical trials in people with dementia (27) and Parkinson's disease (30). Moreover, nabilone is a THC analog; THC appears to reduce anxiety at low doses but becomes anxiogenic at high doses. Thus, administering nabilone at lower doses is theoretically consistent with the treatment objective for SBP.

Participants will be then on a stable, optimized nabilone dosage for four weeks, and then the trial ends with an on-site termination visit (V1). During the open-label trial phase, the study team will call the participant and their caregivers once weekly to perform a basic check-up, and to follow up with any questions or concerns from the trial processes. If there are any changes suspected to be associated with AEs, the UKU side effect rating scale will be assessed during the telephone check-up.

At V 1, the following post-treatment assessments will be completed:

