- 8) Adults currently taking other cannabinoids, such as CBD or medical cannabis, from another source, unless participants and/or their caregivers are willing to stop this treatment for at least 4 weeks prior to entering the study.
- 9) Adults who might travel out of the area for a significant time during the study.
- 10) Adults who recently are participating in another investigational drug trial.
- 11) Pregnancy.
- 12) Sexually active women of child-bearing potential intended to give breastfeeding or to get pregnant.

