## **7.2. Stopping of parts of the study**

If participants fail to discontinue the use of any cannabinoids or high doses of benzodiazepine (more than the benzodiazepine equivalent to lorazepam 2 mg daily), psychostimulants for attention-deficit hyperactivity disorder (ADHD), and nonbenzodiazepine hypnotics 4 weeks before the start of the titration phase, they will not progress to the Pre-Treatment visit (V 0). We will discuss with participants and their caregivers to confirm their willingness to further proceed with the study. The participants are only permitted to proceed with the trial when they do not fulfill this exclusion criterion of the concurrent use of other cannabinoids and high dose of benzodiazepine.

If participants cannot, or are unwilling to, comply with the procedures of NIH Toolbox® Cognition Battery, but can comply with the remaining parts of the study, we will stop assessing them using this cognitive battery. These participants will still proceed with the other parts of the entire studies.

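### Women screened in person have no scheduled pregnancy test at V 0, the last visit before nabilone starts, although women screened virtually do

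*Protocol*

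**What the plan says.** **When the test is done.** Protocol Section 3.3, inclusion criterion 4: "Sexually active women of child-bearing potential must have a negative urine pregnancy test at the screening visit". The screening list in Section 3.2 repeats it: "Urine pregnancy test for sexually active women of child-bearing potential". The baseline list in that section has no such item. Table 1 marks the pregnancy row under Screening only, whereas physical examination, vital signs and weight are marked again at V 0.

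**The virtual exception.** For people who choose virtual screening, Section 3.2 (Elective Virtual Assessment) says of the measures that need attendance: "i.e., pregnancy test, height, vital signs and physical examination) will be carried out in combination with those implemented during the pre-treatment assessment (V 0".

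**When dosing starts.** Section 3.1: "After V 0, eligible participants will receive open-label nabilone starting with a dosage of 0.25 mg before sleep".

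**The cannabinoid washout.** Exclusion criterion 8 rules out current users of other cannabinoids "unless participants and/or their caregivers are willing to stop this treatment for at least 4 weeks prior to entering the study". Section 7.2 deals with those who have not stopped in time: "4 weeks before the start of the titration phase, they will not progress to the Pre-Treatment visit (V 0". It adds that participants are "only permitted to proceed with the trial when they do not fulfill this exclusion criterion of the concurrent use of other cannabinoids". The footnote under Other measures in Section 3.4 also counts the 4 weeks back from the start of study drug.

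**Other protection against exposure in pregnancy.** Inclusion criterion 5 requires contraception from before screening until a month after the study ends. Exclusions 11 and 12 cover pregnancy and the intention to become pregnant. Section 7.1 lists pregnancy among the examples of grounds for withdrawal.

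**The concern.** A pregnancy test at entry is meant to show that a woman is not pregnant when she takes the first dose. It does that only if it is done close to that dose. Here its timing depends on visit format: a virtual screen puts the test at V 0, while an in-person screen leaves it at S-V, with no stated limit on how long ago that was. The protocol gives no reason for the difference.

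At stake is a pregnancy that begins between S-V and the first dose, for example after contraceptive failure or an undisclosed lapse. The protocol treats pregnancy both as an exclusion and as a reason to withdraw, yet for women screened in person nothing scheduled would reveal it before nabilone is taken. This is a safety matter only; no endpoint or analysis depends on it.

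**Working it through.** The plan gives no figure for the age of the test, so there is none to reproduce. The check is a comparison of visit rules followed by date arithmetic.

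**Step 1: the two routes side by side.**

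| Route | Scheduled test | Repeat before first dose | Source |
|---|---|---|---|
| In-person screening | S-V | none | Inclusion 4, Section 3.2 lists, Table 1 |
| Virtual screening | V 0 | none needed | Section 3.2, Elective Virtual Assessment |

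The virtual route also departs from the literal wording of criterion 4, which ties the test to the screening visit.

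**Step 2: the general in-person gap.** Test age at first dose = (S-V to V 0 interval) + (V 0 to first dose interval). The readable text sets no maximum for either. The age is therefore unbounded in the text but could be only a few days for most women. Figure 1, whose caption says that it covers visits and timelines, is not shown and may limit the first interval.

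**Step 3: the washout case, where a minimum follows.**
- Input: washout of at least 4 weeks = 4 × 7 = 28 days, counted back from the start of titration (Section 7.2; Section 3.4 footnote).
- Input: the stop is a condition for reaching V 0, not for attending S-V (Section 7.2). Consent is taken at the screening appointment (Section 5), so stopping for the trial at or after S-V is a permitted and natural order of events.
- Formula: if cannabinoids are stopped *d* days after S-V (*d* ≥ 0), test age at first dose ≥ *d* + 28 days.

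| Stop, days after S-V | Minimum test age at first dose |
|---|---|
| 0 | 28 days |
| 7 | 35 days |
| 14 | 42 days |

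**Step 4: how many women.** The documents do not say. Purely as an assumption, let 10% to 30% of the 40 enrolled be women under criterion 4 who are screened in person: 0.10 × 40 = 4 to 0.30 × 40 = 12. Let 0% to 25% of these stop cannabinoids at or after S-V: 0 × 4 = 0 to 0.25 × 12 = 3. The group with the long gap is then 0 to 3 women.

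**Step 5: after the change.** With a test at V 0, the last test dates from V 0 on both routes.

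**The case against.** The strongest reply has three parts.

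*The long gap may not arise.* Exclusion 8 places the stop before study entry, which can be read as before S-V. A stop before S-V satisfies Section 7.2 and the Section 3.4 footnote as well, and telephone contact before screening could tell a user of the rule in time. Figure 1 might also set an S-V to V 0 window shorter than 28 days. This stands as a limit: the text permits a stop after S-V but does not require one, and the figure cannot be checked. It does not remove the difference between the two routes in Step 1.

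*Other controls cover the interval.* Contraception is required throughout, pregnancy is an exclusion without a time limit, only eligible participants are dosed, V 0 includes a physical examination, and nothing prevents a retest if one is clinically indicated. This lowers the risk considerably. But the contraceptive methods named in criterion 5 (abstinence or an oral hormonal product) depend on behaviour and accurate reporting, and the exclusion and withdrawal rules act only on a pregnancy that is already known. None of them schedules a test.

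*A V 0 test does little for the weeks on treatment.* True. Conception after V 0 would still rely on contraception. The point concerns only the status at first dose.

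A reader might also infer that every woman screened in person starts on a test at least four weeks old. The documents do not support that: the 28-day minimum applies only to a stop at or after S-V, and others may move to V 0 quickly. Nor does it extend to people above the benzodiazepine, stimulant or hypnotic limits. Section 7.2 mentions these drugs, but exclusion 7 excludes such users at screening with no option to stop and wait.

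**Conclusion.** The point holds in a limited form. For women screened in person, the readable protocol schedules one pregnancy test, at S-V, with no repeat and no maximum interval before dosing. For women screened virtually, it places the test at V 0. Where other cannabinoids are stopped at or after S-V, the test is at least 28 days old at first dose, and 28 + *d* days if the stop comes *d* days later.

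This rests on two conditions: that exclusion 8 is read together with Section 7.2 and the Section 3.4 footnote as allowing a stop after screening, and that Figure 1 sets no shorter S-V to V 0 window. The number of women with the long gap is small and may be zero; the range of 0 to 3 comes from assumed percentages and should carry no weight beyond that.

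It would go too far to say that the protocol leaves pregnancy uncontrolled or that exposure is likely. Several rules reduce the risk, and harm would need a contraceptive failure or lapse within a narrow interval. No endpoint is touched. This is a low-severity safety improvement, worth making because it is simple and the protocol already uses the better time point for one group.

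**What to change.** In inclusion criterion 4 and Table 1, add a negative urine pregnancy test at V 0, before nabilone is dispensed, for every woman to whom the criterion applies. Keep the S-V test for in-person screening, so that a woman already pregnant is found before any washout. Add the test to the baseline list in Section 3.2. This also brings criterion 4 into line with the virtual-assessment text.

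The cost is protocol wording, one more mark in Table 1 and one urine test per woman screened in person, at a visit that already has in-person procedures. On the assumption in Step 4, that is 4 to 12 repeat tests. Women screened virtually need no extra test. The downside is an occasional screen failure found late, at V 0.
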